#### Confidentiality {27}

All research staff and investigators will be employed by the District Health Board and will comply with its confidentiality practices. All participants will be allocated a unique non-identifiable study number and any information disseminated in journals or conferences will ensure patient anonymity is maintained.

#### Plans for collection, laboratory evaluation and storage of biological specimens for genetic or molecular analysis in this trial/future use {33}

There is no planned collection of biological specimens for this study.

### Statistical methods

#### Statistical methods for primary and secondary outcomes {20a}

The primary and secondary outcome data gathered from patients in each study group will be pooled and summarised. The mean, standard deviation and 95% confidence intervals will be calculated for each measure in each group. All outcome measures will be assessed on their distribution and homogeneity to confirm the appropriate statistical model. A mixed-effects linear model will be used to compare longitudinal outcomes between the FA TKA (intervention) to the MA TKA (control), with pre-operative measures as a covariate. Adjustments will be made for multiple testing over time. Pairwise comparisons will be examined using a paired *t*-test if normally distributed or non-parametric test for skewed distribution. Categorical data will be evaluated using frequency and percent distributions, with significance testing performed using Fisher exact test or chi-squared test. Statistical significance is defined as a *p*-value < 0.05. Clinical significance will be assessed against the MCID and the PASS as defined in Orr et al. [42].

#### Interim analyses {21b}

Interim analysis will be conducted at milestones of 6-month and 1-year follow-up for dissemination of results. Periodic analysis will also be conducted for patient safety.

#### Methods for additional analyses (e.g. subgroup analyses) {20b}

Sub-group analysis based on patient phenotype will be dependent on sufficient post hoc sample size calculations.

#### Methods in analysis to handle protocol non-adherence and any statistical methods to handle missing data {20c}

A *per-protocol* and *intention to treat* analysis will be performed. In the event of randomisation errors, the participant will be converted to the study arm that represents the received treatment. The statistical model will be corrected in the event of missing data and to avoid type I error when performing multiple comparisons.

#### Plans to give access to the full protocol, participant level-data and statistical code {31c}

The full protocol is described here and will be summarised in future publications. Only the sponsor and site will have access to the participant-level dataset. The datasets analysed during the current study and statistical code are available from the corresponding author on reasonable request for the purpose of meta-analysis.

### Oversight and monitoring

#### Composition of the coordinating centre and trial steering committee {5d}

The sponsor will routinely monitor the progress of the trial and be responsible for the maintenance of ethics correspondence, governance and compliance documentation and data management. The principal investigator will be responsible for execution of GCP, delegation of authority to research staff and will review adverse events and protocol deviations. A trial steering committee will consist of the principal investigator, co-investigators, research coordinators/assistants and head physiotherapist. Routine meetings will be established to review any major adverse events or protocol deviations. A project sponsor team will also meet quarterly to review progress.

#### Composition of the data monitoring committee, its role and reporting structure {21a}

The principal investigator will review all adverse event forms for safety assessment. Any device or treatment related adverse events will be reviewed regularly by the Investigator team and a midpoint assessment of patient report outcomes will be conducted.

#### Adverse event reporting and harms {22}

An adverse event (AE) is defined as any undesirable clinical occurrence in a participant, whether it is considered to be device related or not, that includes a clinical sign, symptom or condition and/or an observation of an unintended technical performance or performance outcome of the device. A serious adverse event (SAE) is an adverse event that results in hospitalisation or prolongation of existing hospitalisation, persistent or significant disability or incapacity, life-threatening or death. All SAEs will be reported directly to the sponsor after review by the principal investigator for severity, seriousness and relationship to the surgical technique or device. Any event that is potentially associated with the surgical technique or device shall be reported to the local regulatory authority (MedSafe NZ) and the Health and Disability Ethics Committee by the sponsor. All series adverse events will be periodically examined using an alert in the participants electronic medical records and will be reviewed periodically in-line with the evaluation schedule.

#### Frequency and plans for auditing trial conduct {23}

The sponsor will conduct routine monitoring visits through the duration of the study. Yearly progress reports will be provided to the Northern B Health and Disability Ethics Committee.

#### Plans for communicating important protocol amendments to relevant parties (e.g. trial participants, ethical committees) {25}

Annual progress reports will be submitted to the Northern B Health and Disability Ethics Committee. Any substantial changes to the protocol or consent will be communicated to participants at their next follow-up visit. All investigators will be informed of future amendments and are required to sign-off on the current version of the protocol.

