### Eligibility criteria {10}

The inclusion criteria are as follows:The patient is a male or non-pregnant female between the ages of 40 and 80 yearsThe patient requires a primary total knee replacement and is indicated for robotic-assisted surgeryPatient is deemed appropriate for a cruciate retaining knee replacementThe patient has a primary diagnosis of osteoarthritis (OA)The patient has intact collateral ligamentsThe patient is able to undergo CT scanning of the affected limbThe patient has signed the study specific, ethics-approved, informed consent ocumentThe patient is willing and able to comply with the specified pre-operative and post-operative clinical and radiographic evaluations

The exclusion criteria are as follows:The patient has a history of total, unicompartmental reconstruction or fusion of the affected jointPatient has had a previous osteotomy around the kneeThe patient is morbidly obese (BMI > 41)The patient has a deformity which will require the use of stems, wedges or augments in conjunction with the Triathlon Total Knee SystemThe patient has a varus/valgus deformity ≥ 15°The patient has a fixed flexion deformity ≥ 15°The patient has a neuromuscular or neurosensory deficiency, which would limit the ability to assess the performance of the deviceThe patient has a systemic or metabolic disorder leading to progressive bone deteriorationThe patient is immunologically suppressed or receiving steroids in excess of normal physiological requirementsPatient has a cognitive impairment, an intellectual disability or a mental illnessThe patient is unable to speak EnglishThe patient is pregnantThe patient has metal hardware present in the region of the hip, knee or ankle (as this is known to create geometrical distortion in the region of the implant)

All patients will be screened by the orthopaedic consultant surgeon and research coordinator based on the criteria. Patients that meet these criteria and express an interest in participating will be provided an ethics approved patient information sheet following initial consultation with their treating doctor. This sheet provides more detail about the study, potential risks and requirements for follow-up. The research coordinator will assist in scheduling their pre-operative visits if the patient decides to participate in the study. Pre-operative visits include the collection of consent, CT scan, x-rays and completion of patient reported outcomes.

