### Who will take informed consent? {26a}

Informed consent will be obtained by either the orthopaedic consultant surgeon or the research coordinator, both of whom are trained in the study requirements and will be appropriately onboarded. Consent will be collected at the pre-operative radiology visit which is scheduled up to 6 months before surgery, but normally occurs within 4 weeks of admission. Māori cultural support is also available as per the New Zealand ethics guidelines.

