### Outcomes {12}

All participants will undergo assessment by the research team pre-operatively, and at 6 weeks, 6 months, 12 months and 24 months post-operatively. The research team will assist in the randomisation process and cannot be blinded to the allocation. The FJS, OKS, IKSS, KOOS, EQ-5D-5L, Net Promoter, BPI, PSQ and VAS pain are all validated clinical assessments of patients undergoing TKA [10, 32–38]. Physiotherapists will also record functional measures of recovery during in-patient stay and will be blinded to the allocated alignment. The functional measures were selected from recommended list as described by Dobson et al. [39] and include: 4 X 10 m walk test, passive and active range of motion, 30-s sit-to-stand test and a 3-step stair ascend and descend test. A breakdown of outcome measures is displayed in Table 1.

**Table 1 Tab1:** Participant evaluation schedule

Evaluation	History/pre-op	Intra-op	In-patients	6 weeks	6 months	12 months	24 months
Demographics	X						
Medical history	X						
CT scan	X						
Surgical details		X					
Physiotherapy functional tests			X	X			
Recovery				X			
BPI	X		X	X			
PSQ	X						
Satisfaction					X	X	X
Net promoter					X	X	X
OKS	X			X	X	X	X
IKSS	X						X
FJS-12				X	X	X	X
KOOS	X						X
EQ-5D-5L	X			X	X	X	X
VAS pain	X			X	X	X	X
AP and ML X-ray	X						X
Long leg X-rays	X					X	

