### Participant timeline {13}

Participants will be recruited from North Shore Hospital, Auckland and the Elective Surgery Centre, Auckland. Based on other randomised control trials performed at this site [40], this trial aims to recruit 12 patients per month. The recruitment process is estimated to take 22 months and began in November 2020. Results are anticipated in December 2025.

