## Trial status

This is protocol version 3.0 dated 9 April 2021. Recruitment began in November 2020, and two amendments were submitted regarding the wording in the patient information, consent and patient evaluation schedule following the first 10 patients screened by the lead investigator. Recruitment is estimated to be completed by June 2022.

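### The amendment rule makes no exception for participants awaiting surgery: read literally, they would hear of a substantial protocol or consent change only after the operation

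*Protocol article*

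**What the plan says.** The section on communicating protocol amendments {25} gives one timing for telling participants: "Any substantial changes to the protocol or consent will be communicated to participants at their next follow-up visit". It covers every substantial change, names consent changes expressly, and does not separate participants awaiting surgery from those already operated on. The same section requires investigators to be informed of amendments and to sign off the current protocol version.

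Three other places determine what this timing means in practice:

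- **Who will take informed consent? {26a}:** consent is taken at the pre-operative radiology visit, which is "scheduled up to 6 months before surgery, but normally occurs within 4 weeks of admission".
- **Eligibility criteria {10}:** "Pre-operative visits include the collection of consent, CT scan, x-rays and completion of patient reported outcomes". Consent and baseline data therefore belong to the same set of pre-operative visits.
- **Outcomes {12}:** "All participants will undergo assessment by the research team pre-operatively, and at 6 weeks, 6 months, 12 months and 24 months post-operatively". Table 1 has a single pre-operative column, then intra-operative and in-patient columns, then the four follow-up visits.

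**The concern.** The trial compares two ways of performing a single operation that cannot be undone. A participant can act on new information about the trial fully only between consent and surgery. A rule tied to the next follow-up visit suits people already in follow-up. For those still waiting, the next visit of that kind falls after surgery.

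If a substantial change to the consent information were made in that window and the rule were followed as written, these participants would have the allocated technique on superseded information. That bears on whether their consent is valid and, if the change concerned safety, on their protection. The situation is not far-fetched. The Trial status section reports that, with recruitment already under way, "two amendments were submitted regarding the wording in the patient information, consent and patient evaluation schedule". The plan also provides for periodic safety analysis {21b} and regular review of device- or treatment-related events {21a}, either of which could prompt a further change.

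**Working it through.** The plan gives no figure on this point, so there is nothing to reproduce. The check sets the timing rule against the consent window and the visit schedule, then sizes the window.

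**Inputs**

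- Timing rule: next follow-up visit (section {25}).
- Wait from consent to surgery: normally within 4 weeks, at most 6 months (section {26a}).
- Follow-up visits: 6 weeks, 6, 12 and 24 months after surgery (section {12}, Table 1).
- Recruitment: "this trial aims to recruit 12 patients per month" (section {13}).

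**Step 1: which visit comes next for a waiting participant?** After the pre-operative column, Table 1 lists the operation, the in-patient stay and the 6-week visit. No scheduled contact lies between the pre-operative visits and surgery. The next follow-up visit is the 6-week one. Even if the in-patient assessment were counted as follow-up, it too comes after the operation.

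**Step 2: how long could a waiting participant go without being told?** For a change made just after consent, the delay is the wait for surgery plus 6 weeks:

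- usual case: 4 + 6 = 10 weeks;
- longest case: 26 + 6 = 32 weeks, taking 6 months as 26 weeks.

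A change made later in the wait gives a shorter delay, but the scheduled visit still falls after surgery.

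**Step 3: how many are waiting at one time?** The number waiting equals the recruitment rate times the mean wait. With 4.33 weeks to a month, 12 × 4 / 4.33 = 11.1, so about 11. The same section's estimate of 22 months for 240 patients implies 240 / 22 = 10.9 per month, and 10.9 × 4 / 4.33 = 10.1, so the answer hardly moves.

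**Step 4: what of participants already operated on?** The longest gap between scheduled visits is 24 − 12 = 12 months, so someone just past the 12-month visit could wait up to 12 months.

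**Step 5: does another section supply an earlier route?** The adverse event section {22} sends events potentially associated with the technique or device to the regulator and the ethics committee, and names no route to participants. The data management section {19} commits to Good Clinical Practice in general terms. Neither alters the timing stated in section {25}.

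**The case against.** The strongest reply is that a follow-up visit naturally means a visit by someone already in follow-up. On that reading the sentence does not address waiting patients at all, and a condensed article may leave their re-consent to the full protocol or the ethics file. The commitment to Good Clinical Practice, and the requirement that investigators sign off the current version, would also mean that the operating surgeon knows of any change before operating.

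Part of this stands. The sentence does not forbid earlier contact, and actual practice at the site may be better than the text. But the sentence speaks of participants without restriction and of any substantial change, including to consent, so it fixes a timing and is not silent. The section on access to the protocol {31c} states that the full protocol is described in the article. An informed surgeon is not the same as an informed participant.

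Several stronger readings are tempting and are not supported:

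- **That participants may be told only at follow-up, or always after surgery.** The text sets a time but does not exclude an earlier one.
- **That a new risk is being withheld.** A risk is one example of a substantial change. The section mentions none, the amendments reported concern wording and the evaluation schedule, and nothing shows that anyone was operated on under superseded consent.
- **That as many as 72 people wait at once (12 × 6).** This needs every wait to last 6 months, against a stated norm of within 4 weeks.
- **That the data of those affected become contestable.** Nothing in the document supports this.
- **That a channel for telling participants of amendments already exists.** The telephone calls in the Recruitment section {15} go to potential participants to confirm enrolment, and the emails in section {18a} are automatic questionnaire reminders.

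**Conclusion.** The point holds as a defect in how the timing rule is worded. Read literally with the consent window and the visit schedule, section {25} places the communication of a substantial change after surgery for anyone who has consented and is waiting. That is about 11 people at any time during recruitment, assuming the target of 12 per month is met and the wait is 4 weeks. Shorter typical waits lower the number and longer ones raise it. The document does not say how often substantial changes would arise, so the number of participants who would actually be affected cannot be estimated. The waiting group exists only until the last operation; the delay of up to 12 months for operated participants continues through follow-up but matters less, because their operation is already done.

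The consequence is for valid consent and participant safety. Sample size, error rates and analysis are unaffected. Because the correction is a short rewording at little cost, it should be made.

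**What to change.** Replace the sentence in section {25} with a rule that separates two kinds of change:

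- Substantial changes that bear on risk or on willingness to take part are communicated promptly to all participants. Those who have consented but not yet been operated on are told before surgery, with re-consent documented where needed.
- Other changes may be communicated at the next follow-up visit.

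If the site already works this way, the edit only brings the text into line with practice. It alters no endpoint, surgical rule or analysis. The cost is occasional extra calls or emails by existing coordinators, and a few participants may reconsider before surgery.

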#### Dissemination plans {31a}

The results of this study will be published in peer-reviewed journals and presented at orthopaedic scientific conferences. Authorship will reflect contribution to the study and interpretation of the results. The principal investigator is responsible for dissemination of the results and the sponsor may only review and offer recommendations to the final wording. Participants will be informed about the results of the trial if they have ticked this option in the consent form.

## Discussion

CT-based robotic arm-assisted surgery is a useful tool to examine surgical alignment philosophies as it provides a wealth of information on patient morphology, as well as high precision to achieve the surgeon defined implant position. This study will utilise this technology to examine MA TKA and FA TKA. To our knowledge, this is the first randomised control trial to compare these two surgical techniques following the expanded alignment boundary limits in the coronal, sagittal and axial planes as described above. It is also unique by the fact that an advanced analytics tool is utilised to assist the surgeon in achieving balance. The multi-surgeon approach, consistency in surgical technique and post-operative care protocols, use of high precision surgical tools and the blinded randomisation will provide low bias in the results. We believe this study will yield high quality evidence to determine the optimal alignment technique to improve patient outcomes in TKA.

## Trial status

This is protocol version 3.0 dated 9 April 2021. Recruitment began in November 2020, and two amendments were submitted regarding the wording in the patient information, consent and patient evaluation schedule following the first 10 patients screened by the lead investigator. Recruitment is estimated to be completed by June 2022.

## Data Availability

Data will be stored securely in a password-protected file on a secure network and is available to all investigators at the site. De-identified line-item data will also be stored on a password-protected cloud server maintained by the sponsor. The final trial data for this protocol can be supplied on request for the purpose of meta-analysis.

## Abbreviations

AE: Adverse event
aMA: Adjusted mechanical alignment
BPI: Brief pain inventory
CT: Computer tomography
FA: Functional alignment
FJS: Forgotten joint score
GCP: Good clinical practice
IKSS: International Knee Society Score
KOOS: Knee Injury and Osteoarthritis Outcome Score
KA: Kinematic alignment
MA: Mechanical alignment
MCID: Minimum clinically important difference
OA: Osteoarthritis
OKS: Oxford Knee Score
PASS: Patient acceptable symptom state
PSQ: Pain Sensitivity Questionnaire
RCT: Randomised control trial
SAE: Serious adverse event
TKA: Total knee arthroplasty
VAS: Visual analogue scale
